### 2.2. Randomization and Blinding

Randomization will be performed using a computer-generated random number list with a permuted block design in a 1 : 1 ratio. Adequate allocation blinding will be ensured by this procedure. After obtaining participant consent, allocation information will be sent to the main investigator at Kyung Hee University Hospital by telephone, and allocations will not be known by the participants or enrolling investigators.

It is almost impossible to blind practitioners due to the nature of the acupuncture intervention; thus they are aware of treatment allocation. Active and sham acupuncture interventions will be conducted as similarly as possible in order to maintain participant blinding. Outcome assessors and statisticians who perform data collection and analysis will all be blinded to participant treatment allocation status. Throughout the study, communications regarding the treatment process will be prohibited.

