### 2.6. Statistical Analysis

Demographic data will be analyzed to identify pretreatment equivalencies and differences between the two groups. Continuous variables will be presented as mean ± standard deviation (SD), evaluated for distribution normalcy, and compared using the Student's *t*-test or Mann-Whitney test wherever appropriate. Categorical variables will be presented as frequencies and percentages and compared using chi-squared or Fisher's exact tests wherever appropriate. AF recurrence during the 12-week follow-up will be analyzed with Kaplan-Meier curves.

Multivariate Cox regression analysis will be performed to determine which factor is most strongly associated with AF recurrence. Serious adverse events will be tabulated per treatment group and analyzed using the chi-squared test.

A *P* value less than 0.05 will be considered statistically significant. All analyses will be performed with SPSS software (Windows version 17.0, Chicago, Illinois, USA) by a statistician blinded to participant allocation.

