### 2.7. Safety and Adverse Event (AE) Outcomes

Safety and adverse event (AE) outcomes are defined as any unexpected or unfavorable symptoms, signs, or diseases that occur during or after treatment, which are not necessarily caused by the treatment. These AEs include local pain, hematoma, bleeding, redness, itching, dizziness, or local infection. All participants and practitioners will be taught to report any AEs. If there are AEs, the following items will be recorded by practitioners at each visit, and appropriate actions will be taken: type of AE(s), occurrence date, lost date, frequency of occurrence, severity, strength of association with the treatment, acupuncture intervention actions taken, and actions taken with respect to the participant. Serious AEs, such as death or life-threatening events which require urgent intervention, will be reported to the principal investigators immediately, who will determine whether the participants will be dropped from the study.

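### Serious adverse events are to be tested by chi-squared alone although the tables may well be sparse; separately, practitioners who know the arm judge adverse-event severity and relatedness

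*Protocol article*

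**What the plan says.** **Test for serious AEs.** Section 2.6 first gives a general rule for categorical variables: chi-squared or Fisher's exact test, whichever suits. A later sentence deals with serious AEs on their own: "Serious adverse events will be tabulated per treatment group and analyzed using the chi-squared test". The threshold is 0.05.

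**Who judges AEs.** Section 2.2 says of the practitioners: "thus they are aware of treatment allocation". Under section 2.7, if AEs occur, "the following items will be recorded by practitioners at each visit", and the items include "severity, strength of association with the treatment". Section 2.1 describes the trial as blinded for participants and assessors. Section 2.2 adds: "Outcome assessors and statisticians who perform data collection and analysis will all be blinded to participant treatment allocation status".

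**Who drops patients.** Section 2.2 says that "allocation information will be sent to the main investigator" by telephone after consent, and that "allocations will not be known by the participants or enrolling investigators". Under section 2.7, serious AEs go at once to the principal investigators, "who will determine whether the participants will be dropped from the study".

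**The concern.** Three things need separating.

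1. Serious AEs are probably among the rarest categorical outcomes in this trial, yet theirs is the sentence that leaves Fisher's test out. Applied as written, it could let a handful of events in one arm be reported as a significant safety difference that an exact test does not support.

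2. Severity and relatedness are judgements. Several of the AEs listed in 2.7 (pain, itching, dizziness) are subjective, and the person judging them has just delivered the active or the sham procedure. Knowledge of the arm can colour the comparison of AE severity and attribution.

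3. Section 2.7 speaks of dropping the patient from the study, not of ending treatment. If outcome data end there, and if those who decide know the arm, loss from the primary comparison could depend on the arm.

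**Working it through.** **Inputs.** From the article: 40 per arm, 1:1 allocation, significance level 0.05, recurrence 35.3% v 69.2%, 33 per arm before dropout (2.5, 2.6). The article states no serious-AE rate, so rates of 1% to 15% are assumed below.

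**Step 1: the plan's own figure.** With pooled variance, two-sided 5% and 80% power:

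n = [1.960·√(2·0.5225·0.4775) + 0.842·√(0.353·0.647 + 0.692·0.308)]² / (0.339)² = 32.9, so 33 per arm, as stated. The 40 per arm follows from 33 × 1.2 = 39.6. There is no safety figure to reproduce.

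**Step 2: when is the table sparse?** With equal arms, the smallest expected count is T/2, where T is the number of patients with a serious AE. T/2 < 5 means T ≤ 9. With T ~ Binomial(80, rate), the probability of that is in the third column of the table in step 4.

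**Step 3: individual sparse tables (40 per arm).** For cells a, b, c, d, the uncorrected chi-squared statistic is 80(ad − bc)² divided by the product of the four margins.

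- 4 v 0: 80(4·40)² / (40·40·4·76) = 4.21, p = 0.040. Fisher: 2·C(40,4)/C(80,4) = 2·91,390/1,581,580 = 0.116.
- 5 v 0: 80(5·40)² / (40·40·5·75) = 5.33, p = 0.021. Fisher: 2·C(40,5)/C(80,5) = 0.055.
- 6 v 1: 80(6·39 − 1·34)² / (40·40·7·73) = 3.91, p = 0.048. Fisher: 0.108.

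Each crosses 0.05 by chi-squared only. Given the total T, the true size of chi-squared at nominal 5% is 0% for T = 2 or 3, 11.6% for T = 4 and 10.8% for T = 7.

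**Step 4: overall type I error.** Sum over all x, y from 0 to 40 of Bin(x; 40, rate) × Bin(y; 40, rate), counting tables with p < 0.05:

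| Assumed rate | Expected total | P(T ≤ 9) | Chi-squared size | Fisher size |
|---|---|---|---|---|
| 1% | 0.8 | about 100% | 0.09% | <0.01% |
| 2.5% | 2 | about 100% | 1.30% | 0.03% |
| 5% | 4 | 99.3% | 4.34% | 0.40% |
| 10% | 8 | 72.3% | 5.87% | 1.68% |
| 12.5% | 10 | 44.9% | 5.61% | 2.20% |
| 15% | 12 | 22.1% | 5.35% | 2.55% |

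Averaged over possible totals, chi-squared is not materially too liberal. The fault lies in particular tables.

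**Step 5: the blinding passages side by side.** Section 2.2 says practitioners know the arm; 2.7 makes them the recorders of severity and relatedness; 2.1 calls the trial assessor blinded. So AE judgement lies outside the blinding. For dropping, 2.2 names one main investigator as recipient of the allocation, and 2.7 names principal investigators, in the plural, as deciders. No sentence says whether these overlap. The groups stated to be blind are participants, enrolling investigators, outcome assessors and statisticians.

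**Step 6: how much dropping could matter.** As an illustration, suppose two patients with recurrence were removed altogether from one arm of 33. Sham: (0.692·33 − 2)/31 = 67.2%, a shift of 2.0 points. Active: (0.353·33 − 2)/31 = 31.1%, a shift of 4.2 points. The planned difference is 69.2 − 35.3 = 33.9 points.

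**The case against.** Several points on the other side are sound.

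- The general rule in 2.6 already provides Fisher's test, so a sensible statistician might use it for serious AEs anyway. That makes the repair easy, but the specific sentence still names one test only.
- It is tempting to call chi-squared invalid at the likely counts. The documents do not support this: no rate is given, sparse tables are near certain only at rates up to about 5%, and overall type I error is at most about 5.9%. Fisher's test is also very conservative (size 0.4% at a 5% rate), a real drawback when looking for harm.
- A reader might infer that those who drop patients know the arm. That requires the main investigator to be among the principal investigators, which is plausible but not stated.
- A reader might infer that the main investigator can foresee the end of a block. Section 2.2 sends allocation information, not the list, and enrolling investigators are not told allocations. This does not stand as a finding.
- The sentence on blinded data collection can be read as covering assessors and statisticians only. So it is in tension with AE recording by practitioners and does not flatly contradict it. Moreover, only serious AEs have a stated between-arm test, and the article exemplifies these as death or life-threatening events, where subjective grading matters least.
- Dropped from the study need not mean excluded from the analysis, and analysis sets may be defined in a plan not shown. The shifts in step 6 are small and rest on an arbitrary number of removals.

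What remains is the single named test, the unblinded AE judgement, and a dropping rule that leaves open who is blinded.

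**Conclusion.** The point holds in limited form and is worth an amendment.

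The serious-AE sentence should not fix chi-squared alone. With 40 per arm, any total of 9 or fewer affected patients gives expected counts below 5. The p-value can then fall on the wrong side of 0.05, as with 4 v 0 (0.040 against 0.116) and 5 v 0 (0.021 against 0.055). How often such tables arise depends on the assumed serious-AE rate. Overall type I error is not materially inflated.

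Unblinded judgement of AE severity and relatedness follows directly from 2.2 and 2.7 and can bias the AE comparison; its size cannot be estimated from the article. Biased retention is a possibility that the wording leaves open, not something the article shows. These are separate matters: the choice of test affects a p-value and cannot bias recording or retention.

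**What to change.** 1. In 2.6, replace chi-squared for serious AEs by Fisher's exact test, with an exact confidence interval for the between-arm comparison. Cost: a more conservative test. The interval helps, because it shows how large a difference in harm remains compatible with the data.

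2. In 2.7, state that patients dropped after a serious AE stay in outcome follow-up and in the analysis as randomised, and state whether those who decide know the allocation. This says nothing about whether or when treatment stops, and no such rule is proposed here. Cost: wording, plus follow-up of a few patients.

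3. Let practitioners write down the occurrence and description of each AE, and have existing blinded trial staff judge severity and relatedness from that written record, with arm and needle site masked. The masking is essential. Active and sham sites differ (Table 2) and sham delivers no current (2.3.2), so examining the skin, or reading an unmasked note, could reveal the arm to those who assess the primary endpoint. Cost: a little more work per AE. One limit remains: practitioners still decide what is written down.

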### 2.3. Intervention

#### 2.3.1. Active Acupuncture Treatment Group

The active acupuncture treatment group will receive two forms of acupuncture: electroacupuncture (EA) and intradermal acupuncture (IDA).

EA treatment consists of 4 acupuncture points (unilateral PC5, PC6, ST36, and ST37, Figure 2) [11]. Disposable, sterile needles (0.20 mm × 30 mm, Dongbang Acupuncture Inc., Boryung, Korea) and a low frequency electrical stimulator (ES-160, ITO, Japan) will be used. Each needle will be inserted to a depth of 2 ± 0.5 cm at a 90-degree angle. Then, the practitioner will rotate the needle several times and induce de-qi (acupuncture-evoked sensations including numbness, heaviness, soreness, or distention). Thereafter, needles will be connected to the pole, and 2 Hz continuous electric current will be applied for 20 minutes. Intensity will be increased until participants feel stimulation but not discomfort, and their muscles twitch slightly.

Four bilateral acupuncture points (HT7 and TF4, the* shen men* points) have been selected for the IDA treatment (Figure 2) [11]. Disposable, sterile, sticker-type needles (0.18 mm × 1.3 mm × 1.5 mm, Dongbang Acupuncture Inc., Boryung, Korea) will be used. Each needle will be applied to a depth of 1 mm at a 90-degree angle. Attached needles will be replaced every visit by practitioners. However, when the needles accidentally fall out (e.g., when washing their hands or face) or the participants feel some discomfort in the acupuncture sites after returning home, participants will be instructed to replace the needles themselves. They will be fully instructed by the practitioners on how to replace the needles on their first visit. Even if the needles do not fall out and the acupuncture sites are not uncomfortable, practitioners will teach participants to replace the needles every two days to prevent infection. Participants also will be taught that repetitive stimulation of manual pressure is helpful.

Acupuncture treatments will be conducted by Doctors of Korean Medicine educated by the College of Korean Medicine for 6 years who are licensed by the Korean Ministry of Health and Welfare and who have more than 3 years of clinical experience. All practitioners will be trained to follow the study protocol.

#### 2.3.2. Sham Acupuncture Treatment Group

During sham treatment, nonacupuncture points (Table 2) will be superficially stimulated. As with the active treatment, two types of sham acupuncture will be performed: sham EA and sham IDA.

For sham EA, 4 nonacupuncture points (Table 2) located 1.5–2 cm lateral to the real acupuncture points will be punctured to a depth of 0.5 cm at a 90-degree angle. Next, the practitioner will connect needles to the pole, and sounds simulating electroacupuncture will be generated, but electrical stimulation will not be delivered. Manual manipulation will not be performed, nor de-qi sensations stimulated.

For sham IDA treatment, 4 nonacupuncture points have been selected. Locations are listed in Table 2. Each needle will be applied to a depth of 1 mm at a 90-degree angle and participants will also be taught identically with active acupuncture group.

All other elements such as needle size, retaining time, frequency and number of treatments, and practitioner will be identical between the two active and sham acupuncture groups.

### 2.4. Outcome Measurement 

#### 2.4.1. Primary Endpoint

Primary endpoint is AF recurrence rate after EC using regular 12-lead electrocardiography (ECG) and 48-hour Holter monitoring. ECG will be conducted at each visit. Whenever patients feel palpitation, symptoms must be registered and patients must be referred to the hospital. AF recurrence is defined as documented 12-lead ECG or AF episodes exceeding 30 seconds during Holter monitoring. 48-hour Holter will be performed at day 1 after EC at baseline and 1 and 3 months post-EC to evaluate recurrence.

#### 2.4.2. Secondary Endpoints

Secondary endpoints are changes in LA and LAA function and volume using 2- and 3-dimensional echocardiography between baseline and 3 months after EC and changes in inflammatory and endothelial biomarkers (i.e., hs-CRP, NT-pro BNP, interleukin-10 (IL-10), and CD40 ligand) between baseline and 3 months after EC. Factors that make AF recur including demographic data, electrocardiographic and echocardiographic data, comorbidities, biomarkers, medications, and CHA2DS2-VASc score will also be investigated irrespective of active or sham acupuncture treatment.

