## 2. Methods/Design

### 2.1. Patient Population and Study Design

This acupuncture in persistent AF (ACU-AF) study will be a multicenter, prospective, participant and assessor blinded, randomized, sham-controlled clinical trial with 2 parallel arms. Two institutes will take part in this study: Kyung Hee University Medical Center and Kangdong Kyung Hee University Hospital. Eighty patients will be enrolled for 2 years. We will compare the efficacy of active acupuncture and sham acupuncture treatments.

Inclusion and exclusion criteria are listed in Table 1. Flow diagram is displayed in Figure 1. The following data will be evaluated at baseline: demographic data, electrocardiographic and echocardiographic data, comorbidities, biomarkers, medications, and CHA2DS2-VASc score. AAD (flecainide 75 mg twice daily) will be administered to patients confirmed with persistent AF lasting more than 7 days. Flecainide administration will be initiated 2 weeks before EC and maintained during the follow-up period. The resistance for flecainide is defined as AF is not converted to sinus rhythm with oral flecainide before EC. Other types of AADs are not allowed, so participants taking other drugs will be required to change their medication to flecainide. Heart rate control drugs will be permitted (calcium channel blockers such as verapamil or diltiazem, except digoxin and beta blocker), and all dose increases or decreases will be determined by an attending physician. Simultaneous anticoagulation therapy with warfarin will be performed to achieve the target international normalized ratio (INR) of prothrombin time (range 2-3) before EC and during the follow-up period. Patients resistant to drug therapy will be randomized into active and sham acupuncture groups through central randomization. After randomization, once-per-week active or sham acupuncture will be initiated 2 weeks before EC.

Transesophageal echocardiography (TEE) will be conducted just before EC to rule out atrial thrombus and evaluate heart function. If any thrombus is present, EC will be delayed for 2 weeks. In this event, TEE will be conducted again after continuous warfarin administration for 2 weeks. If the thrombus disappears in that time, or is not present, EC will be performed.

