## 3. Discussion

This trial was designed to compare active to sham acupuncture efficacy for preventing AF recurrence after EC. Second, to determine which factor is associated with any preventive effects of acupuncture on AF recurrence, changes in LA and LAA volume and function, as assessed by echocardiography and inflammatory biomarkers, will be investigated. We will also use a multivariate Cox regression analysis to investigate factors associated with AF recurrence irrespective of acupuncture or sham intervention.

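### Secondary echo and biomarker changes: baseline adjustment would gain precision at no cost, and 3-month changes should not be presented as explaining the preventive effect

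*Protocol article*

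**What the plan says.** Section 2.4.2 defines the echocardiographic endpoints as changes: "Secondary endpoints are changes in LA and LAA function and volume using 2- and 3-dimensional echocardiography between baseline and 3 months after EC". It defines the biomarker endpoints in the same form: "changes in inflammatory and endothelial biomarkers (i.e., hs-CRP, NT-pro BNP, interleukin-10 (IL-10), and CD40 ligand) between baseline and 3 months after EC".

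Section 2.6 opens with a comparison of the arms at entry ("Demographic data will be analyzed to identify pretreatment equivalencies and differences between the two groups"). It then gives one rule for continuous variables, a comparison by "Student's *t*-test or Mann-Whitney test wherever appropriate". No baseline covariate is mentioned and the secondary endpoints are not named. The only multivariable model described is a Cox model for recurrence.

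Section 2.1 lists echocardiographic data and biomarkers among the baseline data. It randomises only drug-resistant patients and defines resistance by rhythm: "The resistance for flecainide is defined as AF is not converted to sinus rhythm with oral flecainide before EC". Section 2.4.1 provides for a 12-lead ECG at every visit.

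The Discussion (Section 3) gives the secondary endpoints a further purpose: "to determine which factor is associated with any preventive effects of acupuncture on AF recurrence, changes in LA and LAA volume and function", together with inflammatory biomarkers, will be investigated.

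**The concern.** There are two separate matters.

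**Precision.** If the rule in Section 2.6 is applied to the changes in Section 2.4.2, the baseline value is subtracted with a fixed coefficient of 1 and not adjusted for with an estimated coefficient. That is usually less precise. About 32 to 40 patients per arm will be available and no power is claimed for these endpoints, so precision given away matters.

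**Interpretation.** Patients are in AF before cardioversion. By 3 months some will be in sinus rhythm and some in AF. If acupuncture reduces recurrence, the mix may differ between arms. Atrial function, atrial volume and NT-proBNP may then differ because the rhythm differs. A difference that follows from recurrence could be read as the reason recurrence was prevented. The wording of the Discussion invites that reading.

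**Working it through.** **Inputs from the article.** Expected recurrence is 35.3% active and 69.2% sham, with 33 per group required, 20% dropout and 40 per group enrolled (Section 2.5). Allocation is 1:1 (Section 2.2). **Assumed, because the article does not give them:** the baseline/follow-up correlation r and the size of the rhythm effect on the measurements.

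**1. The plan's own figure.** Only the primary endpoint has a sample size. The mean proportion is (0.353 + 0.692)/2 = 0.5225 and the difference is 0.339.

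n = [1.96·√(2·0.5225·0.4775) + 0.8416·√(0.353·0.647 + 0.692·0.308)]² / 0.339² = (1.3845 + 0.5592)² / 0.1149 = 32.9, so 33. The stated figure reproduces. Forty per arm less 20% leaves 32, which is used below.

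**2. Precision.** With equal variance σ² at both times, the per-patient variance is 2σ²(1 − r) for a change score and σ²(1 − r²) for ANCOVA. The ratio is (1 + r)/2. The smallest effect detectable with 80% power, in SDs of a single measurement, is 2.80·√(2v/32), with v = 2(1 − r) or 1 − r².

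| r (assumed) | Variance ratio | Patients per arm giving the precision of 32 | Detectable effect, change score | Detectable effect, ANCOVA | ANCOVA power where change score has 80% |
|---|---|---|---|---|---|
| 0.3 | 0.65 | 20.8 | 0.83 | 0.67 | 93.5% |
| 0.5 | 0.75 | 24.0 | 0.70 | 0.61 | 89.9% |
| 0.7 | 0.85 | 27.2 | 0.54 | 0.50 | 86.0% |
| 0.9 | 0.95 | 30.4 | 0.31 | 0.31 | 81.9% |

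If the variances differ (SD σ₀ at baseline, σ₁ at follow-up), the change-score variance exceeds the ANCOVA variance by σ₀² + σ₁² − 2rσ₀σ₁ − σ₁²(1 − r²) = (σ₀ − rσ₁)². This is never negative. So the direction does not depend on equal variances, but the size does.

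**3. Rhythm.** Suppose acupuncture has no effect on the atrium other than through rhythm, and that every patient with recurrence is in AF at 3 months. The second assumption is an upper bound on the rhythm imbalance. If sinus rhythm shifts the change by δ (in SDs of the change within a rhythm), the expected difference between arms is 0.339·δ. Its variance is [2 + δ²(0.353·0.647 + 0.692·0.308)]/32.

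| δ (assumed) | Difference between arms | Chance of P < 0.05 |
|---|---|---|
| 0.5 | 0.17 | about 10% |
| 1.0 | 0.34 | about 23% |
| 1.5 | 0.51 | about 38% |

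**4. Does ANCOVA help with step 3?** In a simulation (4,000 runs, 32 per arm, r = 0.6, rhythm effect in SDs of a single measurement), the proportions significant were:

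| Rhythm effect | Change-score t-test | ANCOVA |
|---|---|---|
| 0 | 4.7% | 4.5% |
| 0.5 | 11.5% | 12.9% |
| 1.0 | 27.0% | 29.7% |
| 1.5 | 40.9% | 46.3% |

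Baseline adjustment leaves the rhythm effect in place and detects it slightly more often. These are not false positives for the randomised comparison, because the arms do differ. They mislead only if read as the mechanism of prevention.

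**The case against.** The strongest case on the other side is that nothing here is an error.

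- **The test is not assigned to these endpoints.** The rule in Section 2.6 follows a sentence on demographic data, and the article condenses a fuller protocol. An analysis plan may already specify a model. This stands: the rule is the only one stated that fits, but the point is an improvement and not a defect.
- **A change score does use baseline.** A reader might infer that the baseline value is ignored or the comparison biased. It is neither: baseline is subtracted, and under randomisation only efficiency is lost. (Dropping patients after failed cardioversion is a separate matter and bears on both analyses alike.)
- **The size is assumed.** The correlation is in no document. The gain is only 5% at r = 0.9. The ratio rests on equal variances, which a change in rhythm makes doubtful, and it does not describe a Mann-Whitney test or a log-scale analysis. All of this stands.
- **Recurrence is not rhythm at 3 months.** A reader might infer that 3-month rhythm simply restates the primary endpoint. Section 2.4.1 counts a Holter episode of more than 30 seconds as recurrence, so a patient can have recurred and be in sinus rhythm at 3 months. The two are probably related but not the same.
- **Baseline after cardioversion.** Section 2.4.1 has "48-hour Holter will be performed at day 1 after EC at baseline", from which a reader might infer that the secondary endpoints start from a post-cardioversion value. That phrase concerns the Holter schedule. It says nothing about echo or biomarkers.
- **The Discussion claims association only.** This is true of its wording. But the association it seeks is with the preventive effect, and it does not mention that recurrence may itself alter the measurements. The caution survives.

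**Conclusion.** The point holds in two limited parts, both confined to secondary endpoints.

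First, as far as the article states a method, the echo and biomarker changes would be compared without baseline adjustment. That is valid. ANCOVA would need 65% to 95% of the patients for the same precision, for assumed correlations of 0.3 to 0.9 with equal variances. The gain is useful at low or moderate correlation and slight at 0.9.

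Second, changes measured at 3 months come at the end of the window in which recurrence is counted, so they may be its consequences. Under the upper-bound assumption, rhythm alone could make a secondary test significant in about 10% to 38% of trials. These figures illustrate the risk and do not predict it. The problem lies in timing and interpretation, and no choice between a t-test and ANCOVA removes it.

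The primary comparison of recurrence is unaffected.

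**What to change.** 1. In Section 2.6, state that each secondary echo and biomarker endpoint is analysed by ANCOVA of the 3-month value on arm and the pre-randomisation value, on the log scale for skewed biomarkers.
2. In Section 2.4.2, state that baseline means the pre-randomisation measurement. Section 2.1 does not time the baseline echo and blood sample against randomisation.
3. Report the rhythm at the 3-month echo and blood draw, and show the endpoints by rhythm as description only. Rhythm is a post-randomisation result and should not enter the model as a covariate. The randomised comparison over all rhythms stays the analysis of record.
4. In Section 3, reword the aim so that 3-month changes are reported as effects of allocation that may reflect recurrence and are not presented as explaining the preventive effect.

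**Cost.** The change is wording only, provided a pre-randomisation measurement is taken and the 3-month echo and blood draw coincide with the visit ECG. No extra patients or visits are needed. ANCOVA spends one degree of freedom on the slope, which is negligible with about 64 evaluable patients (2 × 32).
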